## Methods

### Study setting and recruitment

The study is taking place from May of 2015 to April of 2018 in smaller primary care practices across three states: Washington, Oregon, and Idaho. H2N is a collaborative partnership between the MacColl Center for Healthcare Innovation at the Group Health Research Institute, Qualis Health in Washington and Idaho, the Oregon Rural Practice Research Network (ORPRN) based at the Oregon Health Sciences University, and the University of Washington’s Institute of Translational Health Sciences. Qualis Health is recruiting practices and providing PF support in Washington and Idaho. ORPRN is recruiting practices and providing PF support in Oregon. The recruitment goal is 250 practices: 120 in Washington, 100 in Oregon, and 30 in Idaho. To be eligible, practices must have 10 full-time or fewer providers in a single location and meet stage 1 electronic health record (EHR) meaningful use criteria. Our rationale for these priority criteria is to focus efforts on smaller practices with the greatest need for externally provided QI expertise and have some capability to produce clinical performance measure reports at the start of the study, given the relatively short 36 months of funding.

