CVD clinical quality measures (CQMs) on each of the ABCS risk factors are being submitted by each practice every 3 months with a 12-month look-back period for each submission. Each practice submits a numerator and denominator for each CQM every 90 days. Three of the CQMs are based on definitions provided by the National Quality Forum (NQF): NQF0068: ischemic vascular disease: appropriate use of aspirin/antithrombotic [23]; NQF0018: controlling high blood pressure [24]; and NQF0028: preventive care and screening: tobacco use: screening [25]. The original NQF cholesterol measure proposed for the study is under revision based on recent changes in evidence-based clinical guidelines. Instead, we are requesting data from each practice on the proportion of patients prescribed a statin who (a) have diabetes; (b) have a history of ischemic vascular disease; or (c) in the absence of either condition have a low-density lipoprotein (LDL) value greater than 190 mg/dl [26].

Practice capacity for QI activities are measured at two time points by the quality improvement capacity assessment (QICA) tool, a practice self-assessment tool used by the facilitators to help practices identify areas where change is needed to improve their capacity to engage in QI. It is a modification of a previously validated tool used to guide primary care practice transformation into a medical home [16]. The single QICA for each practice is completed by the practice team as a group during the first face-to-face visit with their facilitator and again at the fourth of the five face-to-face quarterly visits.

External organizational support for QI is reflected in the growing influence of individual practice relationships with other practices, hospitals, and healthcare systems. Two questions on the practice survey are used to assess this external organizational support: the degree to which the practice is part of a larger organization with a centralized QI team and the autonomy of the practice to choose what QI projects they wish to work on.

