Our analyses will assume intention to treat principles by treating intervention assignment as randomized regardless of whether the intervention had uptake within the practice. We will also attempt to obtain outcome data for all practices even if they stop participating in the intervention. However, there may be some practices that drop-out and stop providing follow-up data. To account for bias due to loss-of-follow-up, we will adjust for baseline practice-level variables that we a priori expect to be related to outcome and may be predictive of loss-to-follow-up. Sensitivity analysis including last value carry forward (follow-up outcome is the baseline outcome for missing practice data) will also be conducted. If loss-to-follow-up is large (>15 %), we will further explore inverse probability of treatment weighting or multiple imputation to handle missing outcome data. We will further conduct subgroup analyses to assess for differential intervention effects (moderators) by baseline practice-level variables including PF support organization, prior practice experience obtaining customized data to drive improvement, prioritization of the work by the practice (high, low), and adaptive reserve (low, medium, and high). Similar analysis will be conducted for secondary outcomes including the other ABCS CQM measures and changes in practice variables such as practice capacity QI.

If we find a difference between any of the four intervention arms, we will conduct a mediator analysis to assess if change in practice capacity for QI was a potential pathway for change in ABCS CQM outcomes. Specifically, we will conduct a mediator analysis following the Barron and Kenny framework [27]. Step 1 is to show that the intervention had an effect of the follow-up outcome. Step 2 is to show that the intervention was associated with change in the potential mediator practice capacity for QI. Step 3 is then to show that the intervention effect is mediated or reduced once the mediator is taken into account. For step 2, we will use a similar linear regression model as outlined for the primary analyses, but the outcome will be the mediator change in practice capacity for QI. For step 3, we will use a similar linear model as outlined for the primary analysis except now further adjust for the change in practice capacity for QI. We will use the method of Sobel [28] to test for the mediator’s indirect effect of the interventions on the ABCS CQM outcome.

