### Sample size

The main aim of the trial is to assess if any of the enhanced practice support arms (site visit, educational outreach, or both) improved ABCS CQM outcome performance relative to practices that received PF alone. If one assumes a 20 % attrition rate over the life of the study leaving 50 practices in each of the four intervention arms, we have 80 % power to detect a 0.114 proportion improvement in any of the three enhanced practice support arms relative to PF for the 1-year practice outcomes blood pressure CQM or aspirin CQM. We assumed an outcome standard deviation of 0.26 for both ABCS outcomes (based on baseline data from the enrolled practices) and a *F* test comparing the four intervention arms assessing for any difference between groups. Further, we used an adjusted sample size calculation for ANCOVA models [29] (proposed analysis adjusts for baseline outcome) assuming a 0.60 correlation coefficient between baseline outcome measure and follow-up outcome measure. Even with an additional 10 % clinic attrition rate (45 practices per arm with follow-up), we will have 80 % power to detect a difference of 0.121 in practice proportion improved in either ABCS outcome. We conducted power calculations via simulation using R version 3.0.2.

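### The weighting method named for missing outcomes models treatment assignment rather than whether a practice reports, and the method for the probably expected level of loss is left open

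*Protocol article*

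**What the plan says.** All references are to the protocol article.

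- **Data analysis, first line of handling.** The investigators will try to obtain outcomes from all practices, including those that stop the intervention. They will adjust for baseline practice variables expected to relate to outcome and possibly to loss.
- **Data analysis, sensitivity analysis.** Carry-forward is defined so that the "follow-up outcome is the baseline outcome for missing practice data".
- **Data analysis, further methods.** "If loss-to-follow-up is large (>15" per cent), then "we will further explore inverse probability of treatment weighting or multiple imputation to handle missing outcome data".
- **Sample size.** "If one assumes a 20 % attrition rate over the life of the study leaving 50 practices in each of the four intervention arms", there is 80% power for a difference of 0.114. A second scenario reads "Even with an additional 10 % clinic attrition rate (45 practices per arm with follow-up"), with 80% power for 0.121.
- **Study setting and recruitment.** The target is 250 practices.
- **Data collection and measures.** "Each practice submits a numerator and denominator for each CQM every 90 days", each report with a 12-month look-back.
- **Data analysis, windows.** Randomisation is in August 2016. Baseline covers July 2015 to June 2016, roll-out runs September to December 2016, and the outcome covers January to December 2017. CQM data covering roll-out are not used for outcome assessment.

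**The concern.** The sentence on further methods states its purpose, which is missing outcome data, but the weighting it names answers a different question. Inverse probability of treatment weights correct for imbalance in who received which arm. The threat here is imbalance in who still reports in 2017, and that needs weights for the probability that the outcome is observed. An analyst who follows the text literally could choose the weighting option alone and leave selective loss uncorrected.

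The trigger matters because of the attrition the plan itself assumes. If the branch reserved for large loss is the one the trial expects to enter, leaving two methods to be explored there means that the choice falls after the loss pattern is known.

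The one sensitivity analysis that is fully specified, baseline carry-forward, fixes a single assumption of no change. It does not show how the result moves as assumptions about lost practices vary.

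**Working it through.** **1. The plan's own figures.** Inputs from Sample size: SD 0.26, correlation 0.60, four arms, omnibus F test. Alpha is not stated, so 0.05 is assumed. The ANCOVA residual SD is 0.26 × √(1 − 0.60²) = 0.208. With one arm differing from the other three, the noncentral F (3 numerator df) gives power 0.805 for 0.114 at 50 per arm and 0.810 for 0.121 at 45 per arm. The stated 80% reproduces.

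**2. Planned loss against the trigger.**
- First scenario: 250 × 0.80 / 4 = 50 per arm, so 50 of 250 are lost (20%).
- Second scenario: 50 × 0.90 = 45 per arm, so 1 − 180/250 = 28% are lost.
- Trigger applied to 250: 0.15 × 250 = 37.5, so 38 or more losses.
- If each of 250 practices is lost independently with probability 0.20, P(38 or more) = 0.98. At 0.28 it exceeds 0.999.
- The article gives no denominator for the 15%. If some loss precedes randomisation, 200 remaining practices are at most 15% post-randomisation loss once 250 − 200/0.85 = 14.7, about 15 practices, have left beforehand. For 180 remaining, the figure is 250 − 180/0.85 = 38.2, about 39 practices.

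**3. What the weights do.** Assume equal allocation, as the equal arm sizes imply. Known assignment probabilities are then the same for every practice, the weights are constant, and the estimate equals complete-case.

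Illustration (assumed inputs, two arms): a binary baseline factor V splits practices evenly. The effect is 0.048 when V = 0 and 0.18 when V = 1, so the average is 0.114. Loss is 20% in both control groups, and 5% (V = 0) and 35% (V = 1) in the active arm, so 20% overall.
- Complete-case, or known treatment weights: (0.95 × 0.048 + 0.65 × 0.18) / (0.95 + 0.65) = 0.1626/1.60 = 0.102 (simulation 0.101).
- Treatment weights estimated from V among reporting practices standardise to the reporting practices. Their V split is 0.95 + 0.80 = 1.75 to 0.65 + 0.80 = 1.45, so (1.75 × 0.048 + 1.45 × 0.18) / 3.20 = 0.345/3.20 = 0.108.
- Adjusting for V as a main effect, with group weights 0.95 × 0.80/1.75 = 0.434 and 0.65 × 0.80/1.45 = 0.359: (0.434 × 0.048 + 0.359 × 0.18) / 0.793 = 0.108.
- Response weights restore the even split: 0.5 × 0.048 + 0.5 × 0.18 = 0.114 (simulation 0.113).

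**4. Interim reports and the roll-out exclusion.** Assuming quarter-end reports, 12-month windows ending September 2016, December 2016, March 2017, June 2017 and September 2017 contain 1, 4, 4, 4 and 3 roll-out months. The windows ending June 2016 and December 2017 contain none. Baseline is thus the last report free of roll-out before the outcome report.

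**5. Baseline carry-forward.** With equal loss in each arm, unrelated to outcome, lost practices contribute no treatment effect:
- 20% loss: 0.80 × 0.114 = 0.091.
- 28% loss: 0.72 × 0.114 = 0.082.

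Standard errors, two arms of 62 at 20% loss:
- Full data: 0.208 × √(2/62) = 0.037.
- Complete-case: 0.208 × √(2/49.6) = 0.042.
- Carry-forward: the baseline slope becomes 0.8 × 0.6 + 0.2 × 1 = 0.68. Residual variance is 0.8 × (0.0433 + 0.08² × 0.0676) + 0.2 × 0.32² × 0.0676 + ½ × 0.2 × 0.8 × 0.114² = 0.0374. The SE is √0.0374 × √(2/62) = 0.035.

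Carry-forward reports more precision than the trial would have had with no loss at all. Effect and SE shrink together: 0.114/0.042 = 2.7 against 0.091/0.035 = 2.6.

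**The case against.** **The weighting term may be a slip of name.** The sentence states the right purpose and offers multiple imputation, which does serve it. Estimated treatment weights are also not inert. With opposite dropout patterns by arm, a prognostic covariate and no effect modification, one illustration moved a complete-case 0.132 to 0.113 against a true 0.114. This stands in part. However, such weights only rebalance covariates among reporting practices, which adjustment for the same covariates already does (both give 0.108 in step 3). They do not restore the randomised set when effects vary.

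**A low trigger is protective, and details may sit in the SAP.** This largely stands. A reader might infer that 15% and 20% contradict each other. They do not: a low threshold only brings further methods in sooner. The 20% is counted over the life of the study, facilitation starts at enrolment, and some loss may come before August 2016. The article may also condense a fuller missing-data plan. What remains is the open choice for a branch that will probably be entered.

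**Carry-forward follows the plan's own rule.** A reader might infer that it throws away quarterly data, for example a report ending September 2017 that shares nine months with the outcome window. The document does not support this. That report also contains three roll-out months, every interim report overlaps roll-out, and the article bars such data from outcome assessment.

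**The first line of handling is sound as far as it goes.** The plan pursues outcomes from all practices and adjusts for baseline predictors of loss. It would be wrong to say that missing outcomes are not addressed.

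**Conclusion.** The point holds in a limited form. The named weighting method does not fit its stated purpose and should be corrected. In the illustration the uncorrected error is 0.114 − 0.101 = 0.013, or 0.006 once the relevant covariate is adjusted for. These sizes depend on assumed loss rates and effect modification; the article gives no data on either.

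The branch for loss above 15% is probably the expected case under planned losses of 20% or 28%, unless about 15 (first scenario) or 39 (second) practices leave before randomisation. Its method should be fixed beforehand, if the SAP does not already do so.

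Baseline carry-forward is permissible and only a sensitivity analysis. Its limits are the zero-change assumption, dilution to about 0.091 at 20% loss, and a standard error that understates the uncertainty.

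Neither the primary model nor the power statement is affected. This is worth correcting before the outcome data are analysed, but it does not put the trial's main analysis in doubt.

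**What to change.** 1. Replace the treatment-weighting term with inverse probability of response (censoring) weights. Model the probability of having the January to December 2017 CQM from arm, randomisation strata, baseline CQM and baseline practice variables.
2. Commit in advance to one method for missing outcomes, for example multiple imputation by arm or response weighting, instead of exploring either once the loss is known. If a percentage trigger is kept, state its denominator.
3. Allow interim quarterly CQMs only as auxiliary variables in the imputation or response model, so that the roll-out exclusion still holds for the outcome.
4. Keep baseline carry-forward if wanted, described as carrying the baseline value forward. Supplement it with a delta-adjusted analysis on the imputations, which shows how far lost practices would have to differ before the conclusion changes.

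The cost is a few lines of wording and modest programming. No new data are needed, and the sample size is unchanged.

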**Fig. 2 Fig2:**
[figure not shown]
Project timeline and data collection windows

For the primary analysis to assess differences between the four intervention groups on the primary outcome practice-level proportion with blood pressure control at 1-year follow-up (blood pressure CQM), we will fit the following linear regression model:$$ {Y}_i={\beta}_0+{\beta}_1{X}_{1i}+{\beta}_2{X}_{2i}+{\beta}_3{X}_{3i}+{\beta}_{\mathrm{base}}{Y}_i^0+{\boldsymbol{\beta}}_z{\boldsymbol{Z}}_{\boldsymbol{i}}+{e}_i\ {e}_i\sim N\left(0,{\sigma}^2\right)\ i=1,\dots, N $$where *Y*
_*i*_ is clinics *i* blood pressure CQM at 1-year follow-up, *X*
_1*i*_, *X*
_2*i*_, and, *X*
_3*i*_ are three indicator variables for intervention assignment for site visit, educational outreach, or both, respectively, *Y*
_*i*_^0^ is baseline blood pressure CQM, and ***Z***
_***i***_ is a vector of other baseline covariates to adjust for differences between clinics including PF support organization (Qualis Health or ORPRN), baseline prior practice experience obtaining customized data to drive improvement (yes, no), and baseline prioritization of the work by the practice (high, low). We will use the Fisher’s protected least significant difference approach to control for multiple comparisons due to the comparison of four intervention arms. Specifically, we will first calculate an Omnibus *F* test to assess if there are any significant differences between intervention groups and only calculate pairwise comparisons if this omnibus test is statistically significant.

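### The mediation model adds the change in QI capacity but does not name baseline QI capacity, which can bias the mediator-outcome slope and the Sobel test

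*Protocol article*

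**What the plan says.** The mediation analysis is described under Data analysis in the protocol article and is run only if the arms differ. It has three steps.

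- **Step 1** shows an intervention effect on the outcome, using the primary model: arm indicators, the baseline blood pressure measure, and a covariate vector Z.
- **Step 2** fits a similar model, "but the outcome will be the mediator change in practice capacity for QI".
- **Step 3** fits a similar model to the primary one, "except now further adjust for the change in practice capacity for QI".

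The Sobel method is then used "to test for the mediator’s indirect effect of the interventions on the ABCS CQM outcome".

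Z names three items: facilitation organization, prior experience with customized data, and prioritization of the work. Baseline QI capacity is not among them. It is available, because the Data collection and measures section says: "Practice capacity for QI activities are measured at two time points by the quality improvement capacity assessment (QICA) tool". The first of those is the baseline assessment at the first facilitator visit.

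**The concern.** Randomization protects the path from arm to mediator. It does not protect the path from mediator to outcome, which depends on covariate control.

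Write M0 and M1 for baseline and follow-up QICA, and D = M1 - M0 for the change. D contains -M0, so practices that start low will tend to show larger gains. If M0 also predicts the follow-up quality measure once D is known, leaving M0 out puts part of its effect into the slope of D. The Sobel test multiplies that slope by the arm effect on D, so the bias carries straight into the indirect effect.

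The Background makes mediation by QI capacity part of the primary hypothesis. A distorted slope could lead the trial to report weak or no mediation where mediation exists.

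**Working it through.** **1. The plan's own figure.** The article gives no figure for the mediation analysis. Its sample size figures do reproduce. With SD 0.26 and correlation 0.60, the residual SD is 0.26 × √(1 - 0.60²) = 0.208. With one arm differing from the other three, the noncentrality is λ = n × d² × 0.75 / 0.208². Alpha is not stated; 0.05 is assumed.

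- n = 50, d = 0.114: λ = 11.26, power 80.5% (stated 80%).
- n = 45, d = 0.121: λ = 11.42, power 81.0% (stated 80%).

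These figures are not in question.

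**2. Slope with baseline capacity left out.** Let Y0 be the baseline quality measure and take the true model as Y1 = b·M1 + c·M0 + g·Y0 + arm effects + error. Since M1 = D + M0, this is Y1 = b·D + (b + c)·M0 + g·Y0 + and so on. The omitted term is (b + c)·M0.

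Let r be the M0-M1 correlation within arm, s the ratio of follow-up to baseline QICA SD, and q the correlation of M0 with Y0. Assume M1 is related to Y0 only through M0. Then

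estimated slope / b = 1 + (1 + c/b) × (rs - 1)(1 - q²) / [s² + 1 - 2rs - (1 - rs)²q²].

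With s = 1 and q = 0 this reduces to (b - c)/(2b), and r cancels. With c = 0 as well, the ratio is exactly 0.50.

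Worked case (s = 1, c = 0, r = 0.6, q = 0.3): 1 - 0.4 × 0.91 / (0.8 - 0.16 × 0.09) = 1 - 0.364/0.7856 = 0.54.

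**3. Range.** The documents give none of r, s, q, b or c. All are assumptions, with r from 0.3 to 0.8 and q from 0 to 0.6.

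| What drives the outcome | QICA SDs | Estimated / true slope |
|---|---|---|
| Follow-up level (c = 0) | equal | 0.50 at q = 0; 0.51-0.57 at q = 0.2-0.4; 0.63-0.67 at q = 0.6 |
| Follow-up level (c = 0) | follow-up 25% larger | 0.66 to 1.00 |
| Follow-up level (c = 0) | follow-up 25% smaller | -0.10 to 0.45 |
| Partial change effect (c = -b/2) | equal | 0.75-0.83 |
| Baseline has an added positive effect (c = +b/2) | equal | 0.25-0.50 |
| Change only (c = -b) | any | 1.00 |

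Combining c = +b/2 with a follow-up SD 25% smaller takes the ratio as low as -0.66.

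**4. Effect on the Sobel test.** An illustrative simulation used 4,000 trials of 4 × 50 practices. It assumed an arm effect on QICA of 0.5 SD, b = 0.08, r = 0.6 and equal SDs. The true indirect effect is 0.5 × 0.08 = 0.040. For c = 0:

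| q | As written: mean indirect effect, Sobel power | Baseline QICA in both models |
|---|---|---|
| 0 | 0.020, 29% | 0.040, about 78% |
| 0.3 | 0.021, 33% | 0.040, about 78% |
| 0.6 | 0.026, 50% | 0.040, about 79% |

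The estimated arm effect on the change in QICA was about 0.50 in every run, with or without baseline QICA. All of the bias is therefore in the mediator-outcome path.

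**5. Price of the extra covariate.** With equal SDs, r = 0.6 and q = 0, the variance of D is 2(1 - 0.6) = 0.80, and given M0 it is 1 - 0.36 = 0.64. If M0 has no role of its own given the change, the standard error of the slope rises by a factor √(0.80/0.64) = 1.12. In the change-only simulations, Sobel power was still higher with baseline QICA in both models (about 79% against 72-75%), because step 2 gained precision.

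**The case against.** **The covariate is not named, but it is not excluded either.** Z is an open list: it "is a vector of other baseline covariates to adjust for differences between clinics including PF support organization (Qualis Health or ORPRN" and two further items. Steps 2 and 3 are only said to be similar to the primary model. For loss to follow-up, the article also says "we will adjust for baseline practice-level variables that we a priori expect to be related to outcome", and baseline capacity could qualify. A journal article may leave a full covariate list to a later plan. This stands as far as it goes, and a reader should not infer that the authors decided against baseline QICA. But the article does write out the step 3 model by naming its one added term, and an analyst following that text would fit the model without baseline capacity.

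**Step 2 is not biased.** Correct. Randomization protects that path, and a similar model may already carry the baseline of its own outcome.

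**The direction and size are not established.** Also correct. A reader might infer that the indirect effect is understated by about half. That figure needs equal QICA SDs, an outcome driven by the follow-up level alone, and at most a moderate correlation between baseline QICA and the baseline quality measure. The article supplies none of these. It speaks of the change as the potential pathway, and if only the change matters there is no bias. By (b - c)/(2b), a c below -b would even give overstatement.

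**The analysis is conditional.** It is run only after an arm difference is found, and the primary test does not depend on it. This limits the weight of the point but does not remove it, because mediation is part of the stated primary hypothesis.

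**Conclusion.** The point holds as a weakness in how the mediation model is specified. As written, step 3 gives an unbiased mediator-outcome slope only in special cases, chiefly when baseline capacity has no effect on the follow-up quality measure given the change. Otherwise the slope and the Sobel product are biased, usually toward zero, and adjusting for the baseline quality measure removes only part of it.

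No single figure for the size can be defended from the article. The ratios in the working run from no bias to a reversed sign, depending on how baseline capacity acts and on whether QICA variability changes between visits. They also assume linear relations, no other mediator-outcome confounder and no measurement error in QICA. Adding baseline QICA removes this source of bias only.

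The primary comparison, the pairwise comparisons and the sample size are not affected.

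**What to change.** Name baseline QICA as a covariate in step 3, alongside the change in QICA. The mediator coefficient is then the same as when follow-up QICA is used with adjustment for baseline, so there is no need to choose between the two forms. Include baseline QICA in step 2 as well, for precision and consistency rather than to remove bias. Compute the Sobel test from these two models.

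The cost is one covariate that is already collected, a sentence in the plan, and a possible small rise in the standard error of the slope from collinearity (about 12% in the case worked above).
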